### Sample size determination:

QIDS-SR-16: Prior studies that have utilized depression rating scales (HAM-D) (Griffiths et al. 2016) have reported within-group effect sizes of 1.30 and 1.23, respectively (with cancer patients with depression and anxiety symptoms). This was with an 82% completion rate of randomized subjects. Additionally, 4 small studies looking at pre-post measures of depression with a psilocybin-assisted therapy intervention (N=69) have demonstrated a pooled standardized effect size of Hedges g 1.38 (Goldberg 2020).

Determining sample size in relation to the MBI and symptoms of burnout is more difficult given less precedent in the literature. Demoralization is a closely related and overlapping concept and Anderson et al. (2020) investigated response to demoralization (Demoralization II Scale) in a psilocybin-assisted group intervention with patients with AIDS. This study demonstrated an effect size (Cohen’s d) of 0.97. Using this effect size and an alpha of 0.05, a sample size of 18 patients would provide 80% power to detect this difference between groups.

We conducted simulation-based power calculations for the linear mixed-effects model. Assuming a **large between group effect size (Cohen’s d = 1.0)**, alpha=0.05, and a **moderate-to-high intra-class correlation (ICC = 0.5)**reflecting the repeated measures design, the estimated power to detect a **treatment group × time interaction** in the LMM was approximately **81%**. Given the pilot nature of this study, the primary goal was to estimate effect sizes and assess feasibility to inform future larger-scale trials.

### Primary Analysis:

- 1. We will track rates of adverse events and rates of serious adverse events utilizing the CTCAE (NCI Common Terminology Criteria for Adverse Events Version 5.0) for adverse events (AE) and serious adverse events (SAE) reporting, as well as the Columbia Suicide Severity Rating Scale (C-SSRS). We will also track qualitative data from participant and clinician direct reporting as well as outcomes with the Challenging Experience Questionnaire (ChEQ).
  2. *QIDS-SR-16:* The analysis of QIDS-SR-16 will use mixed-effects models with fixed effects for time (enrollment, 2 weeks intervention after the last session in each intervention arm), and a random intercept term. The outcome variables are the estimated change from baseline to 2 weeks post completed intervention (full protocol) for both arms. Change from baseline in total score will be analyzed using a generalized linear mixed model (GLMM). A secondary analysis of these scales to determine long term effects of the intervention will include fixed effects at three time points: enrollment, 2 weeks post intervention, and 6 months post psilocybin session.

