| Diagnosis and Main Eligibility Criteria | **Key Inclusion Criteria:**   - Male or female healthcare providers aged ≥ 25 years old. - Participants must be physicians or nurses with at least 1 month of frontline clinical experience during the COVID-19 pandemic. - Screening MBI-HSS (MP) score that meets our working definition of burnout (emotional exhaustion subscale ≥ 27) and a ‘high’ score on one other subscale (either depersonalization ≥ 13 or personal accomplishment ≤ 21). - PHQ-9 depression screen ≥ 10. - Not taking regularly scheduled medications to treat depression and/or anxiety, including benzodiazepines, for at least 4 weeks prior to initiation of the study.   **Key Exclusion Criteria:**   - Prior systemic antidepressants, anti-psychotic, or anxiolytic medication within four weeks prior to psilocybin administration. - Personal history or immediate family members with schizophrenia, bipolar affective disorder, delusional disorder, schizoaffective disorder, psychosis, dementia, or other psychotic spectrum illness. - Currently meeting DSM-5 criteria for Dissociative Disorder, or other psychiatric conditions judged to be incompatible with the establishment of rapport or safe exposure to psilocybin. - Currently meeting DSM-5 criteria for Cluster B Personality Disorder). - Current or history within the last two years of meeting DSM-5 criteria of substance use disorder (excluding caffeine and nicotine). |
| Study Product, Dose, Route, Regimen | Psilocybin 25 mg PO |
| Duration of administration | One-time administration |
| Reference therapy | MBSR |
| Statistical Methodology | Feasibility will be assessed by the ability to recruit, consent, and enroll 24 patients in the trial, and for at least 16/24 patients to remain in the study until completion.  The key secondary analysis of QIDS-SR-16 and MBI-HSS(MP) will use mixed-effects models with fixed effects for time (enrollment, 2 weeks post psilocybin), and a random intercept term. The outcome variables are the estimated change from baseline to 2 weeks post psilocybin from these models. |

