## Number of Patients

This study will enroll a total of 24 patients with 12 patients in each study arm.

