## Statistical Analyses

Aim 1 is to assess the safety and feasibility of MSBR and PAP for burnout. We will track frequency and percentage of adverse events and rates of serious adverse events utilizing the Common Terminology Criteria for Adverse Events (CTCAE) v.5 from study initiation until termination, as well as the Columbia Suicide Severity Rating Scale (C-SSRS). We will also track qualitative data from participant and clinician direct reporting as well as outcomes with the Challenging Experience Questionnaire (ChEQ).

Aim 2 is to assess the efficacy of MBSR+PAP vs. MBSR alone in reducing symptoms of depression, burnout, demoralization, and other clinical symptoms. For continuous outcomes, the analysis will be performed under a generalized linear mixed model (GLMM). The model will include follow-up time as a categorical predictor variable (baseline, 2 weeks, 6 months) as well as the interaction of this categorical factor with the randomized treatment group. Our primary interest lies in the Treatment X Time interaction, expressible as a linear contrast on the β parameters. Repeated effects will incorporate autoregressive dimensioning of the linear predictor, if needed and supported by the Bayesian Information Criterion. In the case that pre-randomization between-groups differences are present in the baseline values of outcome variables, effects will be controlled for chance baseline imbalance using an analysis of covariance strategy that conditions on baseline values. We will use maximum likelihood estimation of missing data for intent-to-treat analyses of all study outcomes.

The statistical model is expressed mathematically as below:

$$Y_{it}=\alpha_{00}+{\alpha_{10}Trt}_{i}+{\alpha_{20}Time1}_{it}+{\alpha_{21}Time2}_{it}+$$

$${\alpha_{30}Trt}_{i}{Time1}_{it}+{\alpha_{31}Trt}_{i}{Time2}_{it}+Z_{i}\beta_{i}+\epsilon_{ijt},$$

$$\beta_{i}\sim N\left( 0, \psi^{2} \right) \left( EQ1 \right)$$

$\epsilon_{it}\sim N\left( 0, \phi^{2}\lambda_{itt} \right), Cov\left( \epsilon_{it}, \epsilon_{it^{'}} \right)=\phi^{2}\lambda_{itt'}$

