### Statistical Power

### Power is based on the efficacy of MBSR+PAP vs. MBSR alone in reducing symptoms of depression. A meta-analysis examining the effects of psilocybin on depressive symptoms reported an effect size of Cohen’s d=1.29. Previous meta-analyses of MBSR indicate modest to moderate effect sizes for depressive symptom reduction (Cohen’s d= 0.3 to 0.4). We conducted simulation-based power calculations for the linear mixed-effects model. Assuming a **large between group effect size (Cohen’s d = 1.0)**, alpha=0.05, and a **moderate-to-high intra-class correlation (ICC = 0.5)**reflecting the repeated measures design, the estimated power to detect a **treatment group × time interaction** in the LMM was approximately **81%**. Given the pilot nature of this study, the primary goal was to estimate effect sizes and assess feasibility to inform future larger-scale trials.

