### Alpha determination:

Miller et al. (2019) discuss a method for estimating the optimal alpha that accounts for base rate (<https://www.ncbi.nlm.nih.gov/pmc/articles/PMC6314595/>). Base rate of depression symptom improvement with mindfulness alone was estimated at 66-76% (<https://www.ncbi.nlm.nih.gov/pmc/articles/PMC2791668/#B5>), based on effect sizes from Khoury et al. (2015). Using this base rate and an anticipated sample size <50, alpha was set at a conventional 0.05. Due to the early phase nature of this trial, we will not correct the alpha level of secondary clinical outcomes for multiple comparisons.

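### The protocol gives two incompatible models for the primary QIDS-SR-16 analysis, one without a treatment term, and adjusts for baseline only if an undefined imbalance appears

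*Protocol*

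**What the plan says.** **Primary Analysis, item 2 (section 12.2).** QIDS-SR-16 is to be analysed with "mixed-effects models with fixed effects for time (enrollment, 2 weeks intervention after the last session in each intervention arm), and a random intercept term". The same item adds: "Change from baseline in total score will be analyzed using a generalized linear mixed model (GLMM"). No treatment term is named.

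**Study Summary, Statistical Methodology.** The analysis of QIDS-SR-16 and the MBI "will use mixed-effects models with fixed effects for time (enrollment, 2 weeks post psilocybin), and a random intercept term". Again no treatment term appears. The time anchor is the psilocybin session, which the MBSR-only arm does not have.

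**Statistical Analyses, Aim 2 (section 12.2).** EQ1 is written out for depression and burnout with treatment, two time indicators and both treatment-by-time products. The text states: "Our primary interest lies in the Treatment X Time interaction, expressible as a linear contrast on the β parameters". α30 is defined as the between-arm difference in reduction from baseline to 2 weeks.

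**Baseline adjustment, same section.** An analysis of covariance is used conditionally: "In the case that pre-randomization between-groups differences are present in the baseline values of outcome variables". No test, size or threshold defines when such a difference counts as present.

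**Related text.** Section 1.1 defines the depression endpoint as a comparison between groups, and the Statistical Power section bases its figure on the treatment-by-time interaction.

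**The concern.** There are two separate faults.

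First, a model with only time and a random intercept estimates one average change across all participants. Both arms receive an active programme and both are expected to improve, so a significant time effect says nothing about whether adding psilocybin-assisted therapy helps. An analyst who follows the Primary Analysis section or the Study Summary would report a different quantity from one who follows Aim 2.

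Second, under randomisation any baseline gap is due to chance, and with 12 per arm some gap will always be visible. A rule that adjusts only when a gap is present leaves the choice between two estimators open until the data are seen. It also gives up precision that the baseline score, already collected, would supply.

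**Working it through.** **Inputs.**
- Sample size (Number of Patients): "This study will enroll a total of 24 patients with 12 patients in each study arm".
- Significance level (Alpha determination): "alpha was set at a conventional 0.05". Sidedness is not stated; two-sided is assumed.
- d = 1.0 and intra-class correlation ρ = 0.5 (Statistical Power).
- No raw QIDS-SR-16 SD is given, so everything is in SD units. No dropout is assumed.

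**1. The protocol's own figure (about 81%).** EQ1 retains α10, a free baseline difference between arms. With complete data α30 is then the unadjusted difference in change scores.
- SD of change = √(2(1 − ρ)) = √(2 × 0.5) = 1.0.
- Standard error = 1.0 × √(2/12) = 0.408.
- Power, normal approximation: Φ(1/0.408 − 1.96) = Φ(0.49) = 69%.
- Power by noncentral t: 65% (22 df) or 67% (44 df).
- One-sided, normal approximation: 79%. Joint 2-df interaction test: 69–72%.

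None of these is 81%. Two other contrasts come close. The baseline-adjusted 2-week contrast and the mean of both follow-ups minus baseline each have SD √0.75 = 0.866, giving 80.7% (normal) or 77.1% (t). The protocol does not say which contrast was simulated.

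**2. The time-only model taken literally.** Its test is the mean change over all 24 participants against zero, with standard error 1.0/√24 = 0.204. Simulated with no difference between arms (40,000 trials):

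| Improvement in both arms | Time effect significant |
|---|---|
| 0.35 SD (within the 0.3–0.4 cited for MBSR) | 38% |
| 1.0 SD | 99.7% |

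**3. Always adjusting for baseline.**
- Residual SD = √(1 − ρ²) = √0.75 = 0.866.
- Standard error = 0.866 × √(2/12) = 0.354, against 0.408.
- Variance falls by 1 − 0.75/1.0 = 25%.

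**4. The conditional rule.** The protocol gives no trigger, so a baseline p-value trigger is assumed (40,000 simulated trials, t-tests):

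| Rule | Power at d = 1.0 | Standard error (SD) | Type I error |
|---|---|---|---|
| Never adjust | 65% | 0.407 | 5.0% |
| Adjust if baseline p<0.05 | 65.2% | 0.396 | 4.3% |
| Adjust if baseline p<0.20 | 66.7% | 0.378 | 3.8% |
| Always adjust | 75% | 0.361 | 5.0% |
| Trigger open, better of the two reported | – | – | 7.2% |

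**5. Sensitivity to the correlation (normal approximation).**

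| ρ | Unadjusted | Always adjusted |
|---|---|---|
| 0.3 | 54% | 73% |
| 0.5 | 69% | 81% |
| 0.7 | 89% | 93% |

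**The case against.** The strongest reply is that the arm comparison is clearly intended. Section 1.1 asks for it, Aim 2 writes the model out for depression, the power statement rests on it, and the Exploratory Analysis describes the mindfulness models as similar to those for depression and as containing treatment factors. On this view the Primary Analysis text is shorthand, and its mention of a GLMM points back to Aim 2. This stands in part. A reader might infer that the trial has no primary test of the arms, and the documents do not support that. What remains is a contradiction, repeated in the Study Summary, about which model is primary.

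The change-score sentence can also be read charitably: the text just before it speaks of an estimated change, which could be a contrast from a model of scores. It is still loose, because enrolment is listed as a time level and change at enrolment is zero by definition.

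On baseline adjustment, the reply is that the harm is mainly inefficiency. That also stands: with a threshold fixed in advance, type I error is 3.8–4.3%, below nominal, and the unadjusted estimate is unbiased over randomisation. The rise to about 7% needs an open trigger and selective reporting.

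Some further criticisms may tempt a reader: that Wald z-tests inflate type I error, that an autoregressive structure wrongly assumes equal spacing, or that baseline is both outcome and covariate. The protocol names no z-test, makes autoregression optional without fixing its form, and does not say that baseline stays an outcome row when covariance adjustment is used. Degrees of freedom and covariance structure can be left to the statistical analysis plan.

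**Conclusion.** The point holds as two limited faults and should be fixed. The Primary Analysis and Study Summary wording is wrong as written, because it contradicts EQ1, the endpoint definition and the power basis. The conditional baseline rule is poorly fixed: at ρ = 0.5 it leaves power at about 65–67% where always adjusting gives 75%, with a standard error about 5–10% larger than it need be. The gain from adjustment is larger at ρ = 0.3 and smaller at ρ = 0.7.

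These figures assume 12 completers per arm, d = 1.0, two-sided 0.05 and, for the conditional rule, p-value triggers that the protocol does not state. They do not show the stated 81% to be wrong: it is not reproduced for the unadjusted 2-week contrast, but it is close to what other contrasts give, and the simulated contrast is not identified.

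**What to change.** - **Study Summary and Primary Analysis, item 2:** replace the time-only and change-score wording with the EQ1 model. Name α30, the difference between arms in change from baseline to 2 weeks post intervention, as the primary contrast.
- **Aim 2:** delete the conditional clause and account for baseline in every case, either by constraining the arms to a common baseline mean (drop α10 from EQ1) or by covariance analysis with baseline always included.
- **Secondary Analysis, item 5:** the same time-only wording is used for additional questionnaires and can be aligned in the same edit.

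The cost is a few sentences and one model specification. No new data, visits or participants are needed.

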### Secondary Analysis:

- 1. *MBI:* Our operationalized definition of burnout is consistent with existing literature and will allow us to track rate of remission in participants. The outcome variable for the MBI is the mean change from baseline to 2 weeks post full intervention and 6 months post intervention. Change from baseline in total score will be analyzed using a generalized linear mixed model (GLMM). In addition, we will examine effects of treatment condition on burnout analyzed as a binary outcome (with participants either surpassing or not surpassing the MBI cut point for burnout: emotional exhaustion subscale ≥ 27; depersonalization subscale ≥ 13; or personal accomplishment subscale ≤ 21).
  2. A secondary analysis will include fixed effects at enrollment, 2 weeks post intervention, and 6 months post psilocybin session
  3. *Demoralization II Scale:* score 0-4 low, 5-16 moderate, 17 and above high. Improvement in 2 points on the 16-item scale is clinically significant. The outcome variable is the mean change from baseline to 2 weeks post full intervention which will be analyzed with a GLMM as described above. Prior studies measuring change on this scale with a PAT intervention suggest an effect size of 0.97 (Anderson 2020).
  4. *PTSD Checklist 5 (PCL-5):* 20-item self-report measure. Will be scored according to total symptom severity score (range 0-80) where a 5-10 point change is seen to represent reliable change and a 10-20 point change is seen to represent clinically significant change. The outcome variable is the mean change from baseline to 2 weeks post full intervention which will be analyzed with the use of a GLMM as described above.
  5. Additional secondary questionnaire efficacy outcome variables will be analyzed using a mixed-effects for time (enrollment and 2 weeks post-completion of group intervention) and a random intercept term. The scales will include the McGill Quality of Life Questionnaire (MQOL) and the Watts’ Connectedness Scale (WCS).

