# STUDY SUMMARY

| Title | PAPR: Psilocybin-assisted psychotherapy (PAP) + Mindfulness-based Stress Reduction (MBSR) for front-line healthcare provider COVID-related depression and burnout. |
| --- | --- |
| Short Title | PAPR |
| Protocol Identifiers (IRB – internal) |  |
| IND number | 163040 |
| Phase | Pilot |
| Design | Open-label, pilot trial. |
| Study Duration | 1.0 years |
| Study Center(s) | This is a single-center trial to be conducted at Huntsman Mental Health Institute |
| Objectives | **Primary Objectives**   - To assess the safety and tolerability of psilocybin in the study population. - To assess the feasibility to recruit, consent, and enroll healthcare providers in a study of psilocybin-assisted therapy + MBSR vs. MBSR and for those participants to remain in the study until completion. - To assess the effect that psilocybin-assisted therapy has on depression symptoms in healthcare providers with burnout as measured by the QIDS-SR-16.   **Secondary Objectives**   - To assess the changes in rates of provider burnout as measured by the Maslach Burnout Inventory for Medical Professionals (MBI-HSS (MP)) both in terms of rates of meeting criteria for burnout as well as mean reduction in score on the MBI. - To assess the long-term effect that psilocybin-assisted therapy and MBSR have on depression and anxiety symptoms in the study population. - To assess the effect psilocybin therapy and MBSR have on symptoms of post-traumatic stress syndrome. - To assess the effect psilocybin therapy and MBSR have on participant reported quality of life. - To assess the effect psilocybin therapy and MBSR have on participant reported feelings of connectedeness to self, other, and world.   **Exploratory Objectives**   - To assess the effect psilocybin therapy, in conjunction with an MBSR curriculum, has on state and trait mindfulness measures. - To assess participant-reported psilocybin experience on the day of medication administration and to assess the relationship between reported experience and depression and burnout response. - To use the Storyline Health AI platform to develop a model for precision research on psychedelic-assisted therapies and healthcare provider burnout and to better characterize predictors of response to mindfulness training and psilocybin therapy utilizing the Storyline Integrative Assessment tool. |
| Number of Subjects | 25 |

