## Secondary Objectives

### To assess the effect of MBSR vs. MBSR+PAP has on the participant-reported symptoms of burnout (as measured by the MBI-HSS(MP)).

*Secondary Endpoint:* The change in mean MBI-HSS(MP) scores from baseline to 2 weeks post intervention with between-group comparison.

*Secondary Endpoint:* The change in mean MBI-HSS(MP) scores from baseline to 6 months post-completion of MBSR intervention.

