**Yes/No Eligibility Questions (Response of “no” = subject ineligible)**

- PHQ-9 score ≥ 10 and meet DSM-5 criteria for a depressive disorder, including adjustment disorder with depressed mood.
- Meet our working definition of burnout which will involve a score on the emotional exhaustion subscale (≥ 27) and a ‘high’ score on one other subscale (either depersonalization ≥ 13 or personal accomplishment ≤ 21).
- Not taking regularly scheduled medications to treat depression and/or anxiety, including benzodiazepines, for at least 4 weeks prior to administration of psilocybin, if randomized to that study arm.
- Fluent in English.
- Reading literacy and comprehension sufficient for understanding the consent form and study questionnaires, as evaluated by study staff obtaining consent.
- Able to provide informed consent and willing to sign an approved consent form that conforms to federal and institutional guidelines.
- ECOG Performance Status ≤ 2.
- Have a support person that would be able to escort the subject home on the evening of the psilocybin dosing session. The use of ride services will not be permitted (e.g., Uber, Lift, taxi, etc.)
- (If randomized to psilocybin arm) Adequate liver function as defined as:
  - Total Bilirubin < 1.5x institutional upper limit of normal (ULN) unless elevated bilirubin is related to Gilbert’s Syndrome.
  - AST(SGOT)/ALT(SGPT) <3 x institutional ULN
  - For female subjects: Negative pregnancy test and agreement to use highly effective contraception or evidence of post-menopausal status if randomized to psilocybin arm. The post-menopausal status will be defined as having been amenorrheic for 12 months without an alternative medical cause.
  - For male subjects: agree to condom use during intercourse for 24 hours post-psilocybin dose.
  - Agree to refrain from using any psychoactive drugs, including alcoholic beverages, ondansetron, cannabis, and non-routine PRN medications within 24 hours of the psilocybin administration. Exceptions include daily use of caffeine, nicotine, and opioid pain medication.
  - Agree that for one week preceding the psilocybin session, he/she will refrain from taking any nonprescription medication, nutritional supplement, or herbal supplement except when approved by the research team. Exceptions will be evaluated by the research team and will include acetaminophen, non-steroidal anti-inflammatory drugs, and common doses of vitamins and minerals.

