In EQ1, $Y_{it}$ denotes the continuous outcome measure for depression or burnout score measured at the $t^{th}$time (t=0, 1, 2 for baseline, 2^nd^ week and 6^th^ month) for the $i^{th}$ participant, $\alpha_{00}$ is the intercept, which is the effect for the MBSR alone group at baseline, $\alpha_{10}$ is the treatment effect difference between MBSR+PAP vs. MBSR alone group at baseline, ${Trt}_{i}$ is a 0-1 indicator variable which takes the value 1 when the $i^{th}$ participant is assigned to the MBSR+PAP group, otherwise 0, $\alpha_{20}$ is the difference between the 2^nd^ week and baseline for MBSR alone group, $\alpha_{21}$ is the difference between the 6^th^ month and baseline for MBSR alone group, ${Time1}_{it}$ and ${Time2}_{it}$ are 0-1 indicator variables which take the value 1 when t=1 (2^nd^ week), t=2 (6^th^ month, $\alpha_{30}$ is the extra treatment effect difference between MBSR+PAP and MBSR alone group when compare the 2^nd^ week to baseline, $\alpha_{31}$ is the extra treatment effect difference between MBSR+PAP and MBSR alone group when compare the 6^th^ month to baseline, $Z_{i}$is a 0-1 indicator variable which take the value 1 for the $i^{th}$ participant, otherwise 0, $\beta_{i}$ is the participant effect for the $i^{th}$ participant, $\psi^{2}$is the variance of the random participant effect ($\beta_{i}$), $\epsilon_{it}$ is the residual at the $t^{th}$time for the $i^{th}$ participant, $\phi^{2}\lambda_{itt'}$ is the covariance between the $t^{th}$ and the ${t'}^{th}$time.

The coefficient of $\alpha_{30}$ is the difference of reduction in depression/burnout from baseline to the 2^nd^ week comparing the two groups, which constitutes the efficacy of the MBSR+PAP. The coefficient of $\alpha_{31}$ are the difference from baseline to the 6^th^ month, which constitutes the long-term effect of the outcome. For outcomes with only two timepoints, the coefficient of $\alpha_{31}$ will be dropped.

In an exploratory analysis, burnout measured as a binary variable (e.g., burnout vs. not-burnout) will be evaluated using generalized linear mixed effects models assuming a binomial distribution with probit (cumulative logistic) link. The probit link gives results very similar to the logit link, but yields a more natural interpretation in terms of an underlying propensity.

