**Total Score: (Range 0–27)**

##### MBI Human Services Survey for Medical Personnel

| **How often:** | **0** | **1** | **2** | **3** | **4** | **5** | **6** |
| --- | --- | --- | --- | --- | --- | --- | --- |
|  | Never | A few times a year or less | Once a month or less | A few times a month | Once a week | A few times a week | Every day |

| **How often ( 0-6)** | **Statements:** |
| --- | --- |
| 1. | I feel emotionally drained from my work. |
| 2. | I feel used up at the end of the workday. |
| 3. | I feel fatigued when I get up in the morning and have to face another day on the job. |
| 4. | I can easily understand how my patients feel about things. |
| 5. | I feel I treat some patients as if they were impersonal objects. |
| 6. | Working with people all day is really a strain for me. |
| 7. | I deal very effectively with the problems of my patients. |
| 8. | I feel burned out from my work. |
| 9. | I feel I'm positively influencing other people's lives through my work. |
| 10. | I've become more callous toward people since I took this job. |
| 11. | I worry that this job is hardening me emotionally. |
| 12. | I feel very energetic. |
| 13. | I feel frustrated by my job. |
| 14. | I feel I'm working too hard on my job. |
| 15. | I don't really care what happens to some patients. |
| 16. | Working with people directly puts too much stress on me. |
| 17. | I can easily create a relaxed atmosphere with my patients. |
| 18. | I feel exhilarated after working closely with my patients. |
| 19. | I have accomplished many worthwhile things in this job. |
| 20. | I feel like I'm at the end of my rope. |
| 21. | In my work, I deal with emotional problems very calmly. |
| 22. | I feel patients blame me for some of their problems. |

(Administrative use only)

EE Total score: ___ DP Total score: PA Total score:

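### The MBI outcome is a total score that the protocol's form does not produce and whose direction is undefined, and the follow-up burnout rule, read literally, conflicts with the entry definition

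*Protocol*

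**What the plan says.** **Continuous outcome.** The Study Summary sets the MBI objective "both in terms of rates of meeting criteria for burnout as well as mean reduction in score on the MBI", so a lower score is taken as better. Section 1.2 gives the endpoint as "The change in mean MBI-HSS(MP) scores from baseline to 2 weeks post intervention with between-group comparison" and names no subscale. Section 12.2, Secondary Analysis, item 1, then states: "Change from baseline in total score will be analyzed using a generalized linear mixed model (GLMM". The appendix form has 22 items scored 0 to 6 and ends with "EE Total score: ___ DP Total score: PA Total score". It has no line for an overall total.

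**Binary outcome.** The same item says that the operationalized definition of burnout will be used to track remission, and gives the cut point as "emotional exhaustion subscale ≥ 27; depersonalization subscale ≥ 13; or personal accomplishment subscale ≤ 21". The entry definition (Study Summary, Section 4.1 and Section 5.1) requires EE ≥ 27 together with one further criterion: "either depersonalization ≥ 13 or personal accomplishment ≤ 21".

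**Model for the binary outcome.** Section 12.2, Statistical Analyses, calls this analysis exploratory and describes a mixed model "assuming a binomial distribution with probit (cumulative logistic) link".

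**The concern.** The Background and the cut-offs both treat low PA as burnout, while high EE and high DP are burnout. A score that adds the three as they stand has no consistent direction: a gain in PA raises it, and falls in EE and DP lower it. Elsewhere the protocol spells out reversal where it is needed, since the scoring formula for the connectedness scale (WCS) contains 100-minus terms. For the MBI it gives none.

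The binary rule as printed is also easier to meet than the rule used to enrol. Remission at follow-up would then not mean ceasing to meet the condition for which the patient was admitted.

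Burnout is in the trial's title, is an entry criterion and is the first secondary objective. A pilot meant to supply effect sizes for later trials could pass on an MBI effect shrunk by its scoring, and a remission rate tied to a different definition.

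**Working it through.** The protocol states no figure for either point, so there is nothing of its own to reproduce.

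**1. How much of the instrument runs the other way.** Items 4, 7, 9, 12, 17, 18, 19 and 21 are positively worded (item 19: "I have accomplished many worthwhile things in this job"). That is 8 of 22 items, so 8 × 6 = 48 of 22 × 6 = 132 points, or 36% of the maximum. This is a share of the scale, not of the expected change.

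**2. Worked patients.** Raw sum = EE + DP + PA. PA-reversed sum = EE + DP + (48 − PA). Entry rule: EE ≥ 27 and (DP ≥ 13 or PA ≤ 21). List rule: any one of the three. All four patients meet both rules at baseline.

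| EE/DP/PA, baseline → follow-up | Raw sum | PA-reversed sum | Entry rule at follow-up | List rule at follow-up |
| --- | --- | --- | --- | --- |
| 30/14/20 → 24/11/29 | 64 → 64 (0) | 72 → 54 (−18) | not met | not met |
| 40/18/24 → 30/12/40 | 82 → 82 (0) | 82 → 50 (−32) | not met | met |
| 35/15/30 → 20/14/30 | 80 → 64 (−16) | 68 → 52 (−16) | not met | met |
| 35/15/30 → 27/10/30 | 80 → 67 (−13) | 68 → 55 (−13) | not met | met |

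The first two patients improve on all three subscales and show no change in the raw sum. The last three no longer meet the entry definition but remain burned out under the list.

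**3. Direction of the misclassification.** Assume 9 EE, 5 DP and 8 PA items. The form shows 8 positive items out of 22; the 9/5 split of the rest is assumed. There are then 55 × 31 × 49 = 83,545 score combinations.
- Entry rule: 28 EE values × (31 × 49 − 13 × 27) = 28 × 1,168 = 32,704 positive.
- List rule: 83,545 − 27 × 13 × 27 = 83,545 − 9,477 = 74,068 positive.
- Disagreement: 74,068 − 32,704 = 41,364 (49.5%, unweighted). In every one the list is positive and the entry rule is not, because meeting the entry rule implies EE ≥ 27.

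In an illustration with follow-up means of 24/10/30, SDs of 9/5/7 and independent subscales, 15% are still burned out by the entry rule and 62% by the list.

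**4. Possible cost to the continuous comparison.** Assume change SDs of 9/5/7, a benefit of 0.8 SD on each subscale, a correlation of improvements from 0 to 0.5, 12 per arm and two-sided alpha 0.05.
- Raw sum: difference 0.8 × (9 + 5 − 7) = 5.6. SD = √155 = 12.45 at correlation 0 and √102 = 10.10 at 0.5. So d = 0.45 to 0.55, power 18% to 25%.
- PA-reversed sum: difference 0.8 × (9 + 5 + 7) = 16.8. SD = √155 = 12.45 at correlation 0 and √298 = 17.26 at 0.5. So d = 1.35 down to 0.97, power 88% down to 63%.

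These effect sizes and powers depend on the assumed SDs and correlations. The table in step 2 does not.

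**The case against.** **Nothing says that PA is left unreversed.** A reader might infer that the plan adds opposing subscales. The protocol says only total score, and its form uses that same phrase for each subscale. The endpoint in Section 1.2 speaks of scores in the plural. The sentence also repeats the one used for the QIDS-SR-16 under Primary Analysis, where a 0 to 27 total exists, so it may simply have been carried over. A SAP that is not shown might reverse PA or use subscales. This stands: cancellation follows from the literal reading but is not established. What remains is that the protocol fixes an outcome its own form does not produce, with no stated direction.

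**The list may be shorthand for the entry rule.** The item opens by invoking the operationalized definition. That is possible, but the printed conjunction contradicts the entry rule, and one must give way.

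**An effect that changes sign.** A reader might infer that the total would reverse a benefit. That needs PA to gain more than EE and DP fall together. The worked cases reach zero and go no further.

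**A binary model that cannot be fitted.** A reader might infer that the model breaks down because everyone is burned out at baseline. Baseline is set as a time level for continuous outcomes; the text does not say that it is an outcome row in the binary model. The MBI is also repeated at week 1, after screening that may be up to 35 days earlier, so baseline need not be uniformly positive. The difficulty is conditional.

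**The link wording.** Probit is cumulative normal, not cumulative logistic. The next sentence distinguishes probit from logit correctly, so this is a slip of wording only.

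**Conclusion.** The point holds in two parts. First, the continuous MBI outcome is a score that the form does not yield, built from subscales that run in opposite directions, with no reversal given. Taken as a plain sum, it can show zero change for a patient who improves by 18 or 32 direction-aligned points. Second, the printed binary rule differs from the entry definition that the same item relies on, and any error runs one way: it understates remission within each arm.

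It does not follow that the contrast between arms shrinks. In the same kind of illustration, means of 26/12/28 against 20/9/32 give 26.6% against 6.9% by the entry rule (19.7 points) and 76.8% against 45.8% by the list (31.0 points). The objection is that the two rules measure different things.

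The worked patients need no distributional assumption. The counts rest on the 9/5/8 item split, and the power figures and percentages on assumed means, SDs and correlations. A must-fix grading is not supported: Section 11.2 makes the QIDS-SR primary and the MBI secondary, the binary analysis is called exploratory, and all subscale scores are already collected. This is a should-fix.

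**What to change.** - In Secondary Analysis, item 1, replace the total score with EE, DP and PA, each analysed separately with its direction of improvement stated. Alternatively, define a total with PA reversed, EE + DP + (48 − PA). Bring the Section 1.2 endpoint into line.
- Define binary burnout, and hence remission, exactly as at entry: EE ≥ 27 and (DP ≥ 13 or PA ≤ 21).
- If the binary model would otherwise include baseline as an outcome row, compare the arms on follow-up status instead, since nearly all participants meet the definition at entry.
- Correct the description of the probit link in Statistical Analyses.

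**Cost.** No new data. Separate subscales mean two extra continuous models. Because the alpha section leaves secondary outcomes uncorrected for multiplicity, they also mean more uncorrected comparisons. A PA-reversed total avoids that, but does not show which subscale moved.
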